**Table: Recruitment rate in previous multi-centre trial (6 vs. 12)**

| Date of TMG   | N centres open | Rate per month from last TMG to current | Rate per month per centre |
|---------------|----------------|-----------------------------------------|---------------------------|
| Sept 2011     | 8              | 2                                       | 0.3                       |
| Dec 2011      | 9              | 6                                       | 0.7                       |
| March 2012    | 10             | 7.7                                     | 0.8                       |
| July 2012     | 12             | 7.3                                     | 0.6                       |
| December 2012 | 15             | 4.6                                     | 0.3                       |

In order to calculate the required sample size, we ran a simulation in which a set of observations from a Poisson distribution with mean 11 were generated. A Chi-squared goodness of fit test of the null hypothesis that these observations were from a Poisson distribution with mean 6 was performed, and rejected if the resulting p-value was equal or less than 0.1. Using a total of 4 observations resulted in power between 95 and 96% with 10,000 replicates. In order to allow enough time for sites to open and collect sufficient data to allow a preliminary assessment of the safety of the deferral of surgery approach and the safety and acceptability of additional pre-operative chemotherapy, the maximum feasibility recruitment period will be 24 months. The primary hypothesis will be tested based on the average rate of recruitment in the four months following the activation of the 12th participating site, or the average rate of recruitment in the final four months of the feasibility recruitment period, whichever is earlier.

## 14. 2 ANALYSIS METHODS

### 14.2.1 PRIMARY ENDPOINT

The primary endpoint of this study is the total numbers of patients randomised per month, during the last 4 months of recruitment. A chi-squared goodness of fit test with one-sided alpha of 0.1 will be used to test the null hypothesis that the expected number of patient recruitment per month is equal to 6. Rejection of the null hypothesis would suggest that recruitment levels are adequate to support the proposed phase III study with sample size and length of recruitment as described in this protocol. However if the null hypothesis is not rejected then exact recruitment rates by time for each centre will be stated, and any known reasons for low recruitment investigated. After taking these results into consideration it may still be deemed possible to proceed with a phase III study if the design is amended accordingly. The primary endpoint for the feasibility study will be stated in full in the phase III protocol before seeking final approval.

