#### **14.1.2 FEASIBILITY STUDY SAMPLE SIZE**

In this feasibility study a type II error would result in the cancellation of the planned phase III study when the recruitment rate was in fact sufficient to support such a study. We wish to minimise the probability of this occurring and so have set the chance of a type II error (B) at 5% and the resulting power (1-B) at 95%. A type I error would result in the planned phase III study going ahead when the true recruitment rate is poor. We would accept a 10% chance of this occurring and so have set the significance threshold (alpha) at 0.1.

The sample size for the primary endpoint of the feasibility study can be worked out as follows:

Recruitment of at least 633 patients to the phase III trial is planned to take place over a total of 3 years, and should take at most no more than 5 years. Hence the recruitment rate is expected to be 11 patients per month and will need to be no less than 5-6 patients per month (5/month results in total time of 6.5 years,

6/month results in 5.5 years total). In a similar multicentre trial sponsored by RM (6 vs. 12), recruitment rates over time were as follows:

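### The primary recruitment test is called one-sided but has no direction, and on four monthly counts it does not give both 10% error and 95% power

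*Protocol*

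**What the plan says.** Protocol section 14.1.2 defines a type I error as going ahead with phase III when true recruitment is poor: "We would accept a 10% chance of this occurring and so have set the significance threshold (alpha) at 0.1". It sets power at 95%. Below the table of recruitment in an earlier trial, it describes the simulation behind the design. There, "a set of observations from a Poisson distribution with mean 11 were generated", a chi-squared goodness-of-fit test of "the null hypothesis that these observations were from a Poisson distribution with mean 6 was performed", and the null was "rejected if the resulting p-value was equal or less than 0.1". The result: "Using a total of 4 observations resulted in power between 95 and 96% with 10,000 replicates". It gives no degrees of freedom, no condition on direction and no simulated type I error. The same section then says the hypothesis is tested on the average rate over four months.

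Section 14.2.1 makes this the primary analysis: "A chi-squared goodness of fit test with one-sided alpha of 0.1 will be used to test the null hypothesis" that the monthly expectation is 6. On the result it says: "Rejection of the null hypothesis would suggest that recruitment levels are adequate to support the proposed phase III study". Section 3.1 separately makes continuation to phase III depend on reaching 6 per month in the last four months of recruitment, and on funding.

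**The concern.** A goodness-of-fit statistic measures distance from the null in any direction. Using its upper tail does not make the hypothesis one-sided. If every rejection is read as adequate recruitment, very slow months and erratic months count as evidence for adequacy, and steady good recruitment can miss the threshold.

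At stake are the error rates of the trial's only primary endpoint, which informs whether a phase III trial of about 633 patients goes ahead. Low rates are not far-fetched: the sponsor's comparator trial in section 14.1.2 ran at 2 per month with 8 centres open.

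**Working it through.** **Inputs (sections 14.1.2 and 14.2.1).** Four monthly Poisson counts; null mean 6; alternative mean 11; reject at p ≤ 0.1.

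**Statistic.** X² = Σ(x − 6)²/6 over four months. The 10% critical values are 6.251 on 3 df and 7.779 on 4 df. The mean of 6 is fixed in advance and the total is not constrained, so 4 df is the right reference.

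**Rejection probability by exact enumeration:**

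| True rate per month | 3 df | 4 df |
|---|---|---|
| 2 | 95.9% | 88.8% |
| 3 | 68.8% | 49.7% |
| 4 | 33.8% | 18.0% |
| 6 (null) | 17.5% | 9.5% |
| 11 (alternative) | 95.8% | 93.0% |

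**The stated power.** The 3-df version reproduces 95–96% (95.8% exact; 96.0% in a 10,000-replicate run). The 4-df version cannot be its source: the simulation standard error is √(0.930 × 0.070/10,000) ≈ 0.26 points, and 93.0% lies 2 points below the band. So the version that gives the stated power has 17.5% rejection at the null, and the version that holds 10% misses the 95% target by 2 points.

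**Direction, by example:**
- 2, 2, 2, 2 (total 8): X² = 4 × 16/6 = 10.67; p = 0.014 (3 df) or 0.031 (4 df). Rejected.
- 2, 10, 3, 9 (total 24, mean exactly 6): X² = (16 + 16 + 9 + 9)/6 = 8.33; p = 0.040 or 0.080. Rejected.
- 9, 9, 9, 9 (total 36): X² = 4 × 9/6 = 6.00; p = 0.112 or 0.199. Not rejected.
- 3, 3, 3, 3 (total 12) also gives 6.00. The test cannot tell it from 9, 9, 9, 9.

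With even counts c, rejection on 4 df needs 4(c − 6)²/6 ≥ 7.779, so c ≥ 6 + √11.67 ≈ 9.4 per month.

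**Adding section 3.1.** Requiring a total of at least 24 as well as rejection, the error at 6 per month is 12.3% on 3 df (11.4% from totals above 24 plus 0.9% at exactly 24) or 7.4% on 4 df (7.0% plus 0.4%). Power at 11 per month stays at 95.8% and 93.0%. At 2 per month the chance of passing both is about 0; at 4 per month it is below 0.5%.

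**A 1-df test on the total T.** Reject if (T − 24)²/24 ≥ 2.706, that is |T − 24| ≥ 8.06, so T ≤ 15 or T ≥ 33. Error is 8.1% and power 96.3%. Erratic counts with mean 6 no longer reject, but at 2 per month it still rejects 99.2% of the time.

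**Exact one-sided Poisson test on T** (null mean 24, alternative mean 44):
- T ≥ 30: error 13.2%, power 98.9%
- T ≥ 31: error 9.6%, power 98.3%
- T ≥ 33: error 4.7%, power 96.3%

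With T ≥ 31 the rejection probability is about 0 at 3 per month and 0.06% at 4 per month.

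**The case against.** Four points can fairly be made for the plan.

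- **Section 3.1 guards the decision.** A trial at 2 per month cannot reach 6 per month, so it would not continue whatever the test says. This stands. The low-rate figures above are probabilities of rejecting the null, not of wrongly starting phase III. A reader might infer that the plan would send a failed trial into phase III; read as a whole, the protocol does not support that.
- **The intent is directional.** Section 14.2.1 says one-sided, and it follows non-rejection with a search for reasons for low recruitment. The intent is clear, but no text turns it into a rule. Adding the missing condition (total above 24) removes the slow-recruitment fault, yet gives 11.4% error with 95.8% power on 3 df, or 7.0% with 93.0% on 4 df. Neither meets both targets.
- **Average rate may mean a 1-df test on the total.** That reading meets both targets even two-sided. Taken one-sided at 0.1 it rejects above 24 + 1.2816 × √24 = 30.3, that is at 31 or more, the rule proposed below. So it would be too strong to say that no reading delivers the stated properties. But it is not the four-count goodness-of-fit test described in the simulation, and without a stated direction it also rejects at totals of 15 or less.
- **The rule is soft, and a statistical analysis plan is promised.** Rejection only suggests adequacy, and discretion is allowed after non-rejection. No safeguard is written for a rejection in the wrong direction. The test, its label and its power are already fixed in the protocol.

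**Conclusion.** The point holds for the test that the protocol names and simulates. That test has no direction: it rejects at a true 2 per month in 88.8% (4 df) or 95.9% (3 df) of cases. It does not combine 10% error with 95% power: the pairs are 17.5% with 95.8% on 3 df, and 9.5% with 93.0% on 4 df.

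The practical harm is smaller than these figures suggest. With section 3.1's criterion applied as a total of at least 24, the false-go error at 6 per month is 12.3% or 7.4%. A reader might also infer that the 95–96% power figure is wrong; it is a true result for 3 df, and what fails is the type I error that goes with it.

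The result assumes independent Poisson counts, as in the protocol's own simulation. That 3 df was used is an inference from the match, since the protocol states no degrees of freedom.

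**What to change.** In sections 14.1.2 and 14.2.1, replace the goodness-of-fit test with an exact one-sided Poisson test on the total randomised in the four-month window. For a null rate of 6 per month, reject if the total is 31 or more: type I error 9.6%, power 98.3% at 11 per month. Restate the power from this test and drop the goodness-of-fit simulation.

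Reconcile the rule with section 3.1. Reaching 6 per month means 24 in four months, whereas rejecting 6 per month means 31, or 7.75 per month. State which governs continuation, or that both must be met. If the null rate is revised, recompute the cut-off.

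The cost is a few sentences of wording. The same four months of data suffice, with no extra patients.

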### 14.2.2 SECONDARY ENDPOINTS

All secondary endpoints will be summarised using descriptive statistics, and will be used to inform the design of the proposed phase III study. The following limited number of endpoints will be summarised by arm, and within arm by patients grouped by mrTRG 1-2 vs. 3-5. Exploratory comparison between arms will be carried out using Fisher's exact test for categorical variables (pCRM rate, proportion with unsalvageable regrowth, proportion of patients with any one or more grade 3-5 toxicity). Quality of surgery and surgical morbidity (maximum Clavien-Dindo grade per patient) will be compared between arms using a Mann-Whitney test. No other formal statistical comparison will be made between arms or mrTRG subgroups for endpoints not listed below.

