### **3.2 RANDOMIZATION METHOD**

Randomization will be in a 2:1 ratio in favour of the mrTRG directed management arm. Randomization will be stratified to avoid differences between arms in important prognostic variables. Stratification variables include:

- recruiting site
- extramural venous invasion on MRI (mrEMVI grades  $\leq 2$  versus  $>2$ )
- tumour height (on MRI, height of tumour from anal verge  $\leq 6$  cm versus  $> 6$  cm)
- the planned choice of systemic chemotherapy (CAPOX/FOLFOX, versus single agent 5-FU/capecitabine)

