## **4.2 SECONDARY OBJECTIVES OF THE FEASIBILITY TRIAL**

### **1. Assess response rate by comparing the reported mrTRG in the control and intervention arm**

Trial participants are randomised with stratification for the key factors that effect response (tumour height, mrEMVI and chemotherapy). Therefore the mrTRG should be similar in the control and intervention arm. In order to avoid the MDT being informed of the mrTRG in the control arm we will report the mrTRG grade in the control arm by centralised assessment. Comparison between the mrTRG in the control versus intervention arm will allow us to evaluate the amount of additional response achieved by using 'upfront' systemic chemotherapy.

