## 5. SITE REQUIREMENTS AND ELIGIBILITY

### 5.1 STUDY SETTING

This is a multicentre trial with an anticipated 10-15 sites being involved in the feasibility stage of the trial. It is also anticipated that a limited number of these sites will be based outside the UK.

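### The between-arm tests in section 14.2.2 ignore the clinical factors that stratify the randomisation, so a chance imbalance passes uncorrected into exploratory comparisons meant to inform phase III

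*Protocol*

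**What the plan says.** Protocol section 3.2 sets the allocation: "Randomization will be in a 2:1 ratio in favour of the mrTRG directed management arm". It gives the purpose of stratifying: "Randomization will be stratified to avoid differences between arms in important prognostic variables". The factors are recruiting site, mrEMVI (grade up to 2 versus above 2), tumour height on MRI (up to 6 cm versus above) and planned chemotherapy (oxaliplatin combination versus single agent). Section 4.2, objective 1, relies on this: "Trial participants are randomised with stratification for the key factors that effect response (tumour height, mrEMVI and chemotherapy"), and concludes that mrTRG ought to be alike in the two arms.

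Section 14.2.2 says how the arms are compared: "Exploratory comparison between arms will be carried out using Fisher's exact test for categorical variables", naming pCRM rate, unsalvageable regrowth and any grade 3-5 toxicity. Quality of surgery and maximum Clavien-Dindo grade "will be compared between arms using a Mann-Whitney test". No stratification factor enters either test. The same section calls the comparisons exploratory, treats the secondary endpoints as descriptive, and says that they will inform the phase III design. It leaves fuller methods to a statistical analysis plan.

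**The concern.** The design identifies factors important enough to stratify on, and the named analysis discards them. Stratifying lowers the risk of imbalance but does not remove it in a trial of 90. Whatever imbalance remains moves the crude difference between arms, and an unstratified test has no means of correcting it.

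The pCRM comparison carries the most weight, because section 4.2, objective 4, describes it as important for judging the safety of mrTRG-directed management. If the intervention arm happens to hold more patients with mrEMVI above 2, its pCRM rate looks worse than it should; if fewer, better. That distorted difference would be carried into phase III planning. The factors that would correct it are already recorded before randomisation.

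**Working it through.** The plan gives no imbalance figure, and no power figure for these comparisons, so there is none to reproduce. Its one feasibility power figure (section 14.1.2) concerns recruitment and is not involved.

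**Inputs from the protocol.** N = 90 at 2:1, so 90 × 1/3 = 30 control and 90 × 2/3 = 60 intervention. There are three two-level clinical factors plus site, with 10-15 sites (section 5.1). Appendix 6 puts EMVI on MRI at 30-40% of rectal cancers; 35% is used here for mrEMVI >2.

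**Assumptions not in the protocol.** Low tumours 40%; single-agent chemotherapy 15%; 12 sites of uneven size; pCRM odds ratios of 4 (mrEMVI >2) and 3 (low tumour); null pCRM rates of 15% or 30%; treatment odds ratios of 0.25 and 0.30 respectively. Allocation is taken as separate permuted blocks of 6 in every crossed cell, the unfavourable case.

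**Step 1: validity.** By enumeration at 30 versus 60, Fisher's true size at nominal 5% is 2.3%, 3.1%, 3.7% and 3.7% for event rates of 5, 10, 20 and 30%. Type I error is not inflated.

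**Step 2: how often imbalance arises.** Under the assumed blocks, the simulated SD of the between-arm difference in mrEMVI prevalence is 9.0 points. By the normal approximation:
- P(intervention excess ≥12 points) = 1 − Φ(12/9.0) = 1 − Φ(1.33) ≈ 9%, with the same chance in the other direction.
- The mean excess in those trials is 9.0 × 0.164 / 0.091 ≈ 16.2 points.

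The same formula gives about 13% under simple randomisation (SD 10.7), 5% with blocks of 3 in every cell (SD 7.1), and under 0.1% with minimisation (SD 3.4) or with blocks of 6 on the eight clinical cells alone (SD 3.8).

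**Step 3: what it does to the pCRM difference.** Let p0 and p1 be the pCRM rates at mrEMVI ≤2 and >2. Then 0.65·p0 + 0.35·p1 equals the overall rate, with p1 = 4·p0/(1 + 3·p0).
- Overall 15%: p0 = 8.5%, p1 = 27.1%, gap 18.6 points. Shift = 0.12 × 18.6 = 2.2 points at exactly 12 points' excess, and 0.162 × 18.6 = 3.0 at the average excess.
- Overall 30%: p0 = 19.6%, p1 = 49.3%, gap 29.7 points. Shift = 3.6 and 4.8 points.

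Simulation including tumour height agrees: a null shift of about 3-5 points when the excess is 12 or more. Stratifying removes it.

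**Step 4: power over all trials, like for like** (4,000 simulated trials per scenario).

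| Test | 15%, OR 0.25 | 30%, OR 0.30 |
|---|---|---|
| Fisher (exact, unstratified) | 33.9% | 42.8% |
| Chi-square (asymptotic, unstratified) | 41.9% | 49.8% |
| CMH over mrEMVI × height (asymptotic) | 41.6% | 53.9% |
| CMH over mrEMVI × height (exact) | 33.3% | 47.2% |

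Asymptotic against asymptotic, stratifying adds −0.3 and +4.1 points; exact against exact, −0.6 and +4.4. A second run of the set-up gave 33/40/40% and 42/49/52% for the first three rows. So the overall gain is about 0-4 points.

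**Step 5: power when the intervention arm has ≥12 points more mrEMVI >2.** The unstratified chi-square has 24% and 35%; CMH has 33% and 54%. Across runs Fisher has 21-22% and 24-27%, and CMH 33-37% and 48-54%. These rest on roughly a tenth of the simulated trials and are correspondingly imprecise.

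**The case against.** **These are exploratory comparisons and nothing is invalid.** This stands. The primary endpoint compares no arms, progression depends on recruitment and funding, and no stated alpha, power, sample size or progression rule changes. It limits the point to a modest one.

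**The SAP can adjust.** In part. Adjusted sensitivity analyses could well sit there. But section 14.2.2 does not leave the tests open: it names them, and an SAP that made stratified tests the main analysis would depart from the protocol.

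**The inputs are assumed.** This stands. The odds ratios and block size are not in the documents. mrEMVI positivity is itself a route into eligibility (section 6.1), so the prevalence of high grades may exceed 35%.

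**Unstratified tests throw away much power.** A reader who sets Fisher beside an asymptotic CMH test would see a gain of roughly 7 to 10 points (33% to 40%, 43% to 53%). Most of that is Fisher's discreteness, as step 4 shows. An exact stratified test returns to Fisher's level in the sparser scenario.

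**The allocation itself fails.** A reader might multiply out the factors: 10 × 8 = 80 to 15 × 8 = 120 cells for 90 patients, or 1.1 to 0.75 per cell, and infer that the balance promised in section 3.2 cannot be delivered. The count is right but the inference is not supported. Sections 3.2 and 7.4 refer only to stratified randomisation; neither says that site is crossed with the clinical factors in separate block lists. Under minimisation on the same factors the cell count is harmless. Even under fully crossed blocks some balance survives: a gap of 15 points or more in mrEMVI or height arises in about 7% (blocks of 3) to 19% (blocks of 6) of trials, against about 30% with simple randomisation.

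**The mrTRG comparison in section 4.2, objective 1, is not repaired.** Correct: section 14.2.2 assigns it no test, so this change does not reach it.

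**Conclusion.** The point holds in a limited form. Section 14.2.2 fixes tests that ignore factors which section 3.2 treats as prognostic. In a trial of about 30 versus 60, a chance imbalance in mrEMVI or height therefore goes uncorrected into the pCRM, quality-of-surgery and morbidity comparisons.

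Its size is modest: a null pCRM shift of about 3-5 points in those trials (about 9% in each direction under the assumed blocks) where the mrEMVI gap reaches 12 points, and only 0-4 points of overall power. The shift rests on the assumed odds ratios, and its frequency on the allocation method: about 5% in each direction with blocks of 3 and under 0.1% with minimisation. The documents do not support a claim of inflated error, of a large general loss of power, or of failed allocation. It is worth changing because the correction is nearly free.

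**What to change.** In section 14.2.2, report the between-arm comparisons stratified by the clinical randomisation factors:

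- **pCRM:** Mantel-Haenszel risk difference with confidence interval and a CMH test over mrEMVI × tumour height (four strata), exact or mid-p if sparse.
- **Grade 3-5 toxicity:** the same approach with planned chemotherapy as a stratum, since it is the factor most directly tied to toxicity.
- **Quality of surgery and maximum Clavien-Dindo grade:** van Elteren test over mrEMVI × tumour height.
- Keep Fisher and Mann-Whitney as sensitivity analyses.

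Site should stay out of the strata: a test over all 80-120 cells is unworkable with 90 patients.

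The cost is a few lines of text and no new data, as every factor is recorded before randomisation. The downside is sparseness. Four strata leave on average 30/4 = 7.5 controls each, and at a 15% pCRM rate only 30 × 0.15 = 4.5 control events in all. Section 14.2.2 also lists the toxicity comparison under poor responders, a smaller set again. Hence the provision for exact or mid-p versions.
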